**Methods:**

This is a hybrid type 3 implementation-effectiveness randomized trial using a scalable evidence-based digital health software platform, NOCTEM™’s Clinician-Operated Assistive Sleep Technology (COAST™). COAST includes a clinician portal and a patient app, and it utilizes algorithms that facilitate detection of sleep disordered patterns, support clinical decision-making, and personalize sleep interventions. The first aim is to compare three clinician- and system-centered implementation strategies on the reach, adoption, and sustainability of the COAST digital platform by offering (1) COAST only, (2) COAST plus external facilitation (EF: assistance and consultation to providers by NOCTEM’s sleep experts), or (3) COAST plus EF and internal facilitation (EF/IF: assistance/consultation to providers by NOCTEM’s sleep experts and local champions). The second aim is to quantify improvements in insomnia among patients who receive behavioral sleep care via the COAST platform. We hypothesize that reach, adoption, and sustainability and the magnitude of improvements in insomnia will be superior in the EF and EF/IF groups relative to the COAST-only group.

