## Objective, aims, and hypotheses

The overarching objective of this investigation is to compare and evaluate three facilitation strategies for implementation (i.e., no facilitation, external facilitation only, and external plus internal facilitation) of the NOCTEM COAST™ platform in MTFs and clinics with a representative sample of ADSMs with common comorbid disorders. The specific aims are to (1) examine and compare the reach, adoption, sustainability, and magnitude of changes in a patient’s sleep for a new patient- and clinician-centered digital platform (COAST) alone, compared to COAST plus external facilitation (COAST+EF) or COAST plus EF and internal facilitation (COAST+EF/IF) in MTFs and affiliated clinics, and (2) quantify the magnitude of improvements in insomnia for patients who receive behavioral sleep care via the COAST platform.

Our first hypothesis is that providers randomized to the COAST+EF or COAST+EF/IF conditions will show greater (a) reach, (b) adoption, and (c) maintenance (sustainability) at 3- and 12-month follow-ups compared to providers randomized to the COAST-only condition. Our second hypothesis is that (a) COAST+EF and COAST+EF/IF will yield greater improvements in insomnia than COAST only over the acute 6-week intervention period, and (b) COAST+EF will not be inferior to COAST+EF/IF as measured by changes on the ISI over the acute 6-week intervention period.

To test these hypotheses, we will enroll at least 24 providers and 864 patients presenting with insomnia who are currently being seen at MTFs, affiliated clinics, and wellness centers across military branches. For an ecologically valid assessment of COAST’s potential to be implemented across facilities of the DHA, we will enroll providers who deliver services to ADSMs with comorbid PTSD, traumatic brain injury (TBI), chronic pain, and other psychiatric and medical conditions that are often comorbid with sleep disorders. The comparison of the three implementation strategies will provide insights into the advantages and disadvantages of each relative to patient- and clinician-centered outcomes. The results will inform anticipated larger implementation efforts across different clinical and operational settings within and outside the DHA.

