## Randomization of providers

After completing the COAST training and 10- to 14-day familiarization period, providers will be randomized in a 1:1:1 manner to one of three implementation strategies: COAST only, COAST+EF, or COAST+EF/IF (implementation strategies are further described below). Providers will be randomized within participating sites to one of the three facilitation conditions. A computer-generated randomization schedule based on a permuted block design will be created a priori. Using a permuted block design ensures that there will be equal numbers in each arm. The allocation will follow the generated sequence and the local research point of contact will inform the providers of their assignment at the end of the familiarization period, prior to patient enrollment.

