## Outcome measures

Table 2 summarizes the schedule of enrollment, interventions, and assessments for participating providers. Clinician-centered, implementation outcomes from the reach, effectiveness, adoption, implementation, and maintenance (RE-AIM) framework [67], see also re-aim.gov, include reach, adoption, and maintenance (sustainability). Provider reach is defined as the ratio of providers who provide informed consent to participate and complete the COAST training over the number of providers who received information about the trainings via emails, personal invitations, and other communication means targeting behavioral health providers. Patient reach is defined as the ratio of patients who consent to use the app relative to the number of patients deemed eligible to use the app. Adoption is defined as the ratio of newly trained providers who initiate the use of the COAST platform with patients (i.e., provide a patient with an app code) over the total number of providers who completed the COAST training (i.e., trained users + trained non-users). Sustainability is determined by comparing the frequency of COAST platform use by the trained providers across the three groups at the 3-, 6-, and 12-month assessments to measure potential changes on these domains over time.

**Table 2 Tab2:** Providers’ schedule of enrollment, interventions, and assessments for this hybrid type 3 implementation-effectiveness randomized trial

			Study period				
	Enrollment	Consent	Baseline	Post-randomization			
**Timepoint**	***-t***_***1***_	**0**	***t1***	***Familiarization***	***3 months***	***6 months***	***12 months***
**Enrollment:**	X						
Complete sleep training	X						
Informed consent		X					
NOCTEM COAST training			X				
Randomization			X				

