The first hypothesis is that providers randomized to one of the two COAST+ conditions will show greater reach, adoption, and sustainability at the 3- and 12-month follow-ups compared to providers randomized to the COAST only. For adoption, we will use a test for two proportions to determine whether reach and adoption differ between COAST versus COAST+EF and COAST+EF/IF at the 3- and 12-month follow-ups. With at least 8 providers in COAST and 16 in COAST+EF and COAST+EF/IF, as well as a reach and adoption between 0.50 and 0.60 in COAST, we will have 0.80 power (alpha = 0.05) to detect a difference in proportions between COAST and COAST+ of 0.39–0.46. For sustainability, each provider’s average number of interactions per patient over time and number of newly enrolled patients each month for each of the 12 months will be computed. We will then fit a generalized linear mixed effects model to regress number of interactions on group (COAST versus COAST+) and time. The group-by-time interaction will also be tested. Models will include a random intercept and time effect. With six repeated measures (autocorrelation 0.60–0.80) and 24 providers (8 COAST and 16 COAST+EF and COAST+EF/IF), we expect 0.80 power (alpha = 0.05) to detect differences of 0.99–1.11 between groups. With 12 repeated measures, we expect power to detect differences of 0.97–01.10 between groups.

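### The implementation analyses pool EF and EF/IF into one group, so as specified they give no arm-specific or EF versus EF/IF estimate, although the aim and the sustainability definition call for a three-group comparison

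*Protocol article*

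**What the plan says.** **What is promised.** The abstract's Methods paragraph gives the first aim as to "compare three clinician- and system-centered implementation strategies on the reach, adoption, and sustainability of the COAST digital platform". The section Objective, aims, and hypotheses says the study will "compare and evaluate three facilitation strategies for implementation" and adds: "The comparison of the three implementation strategies will provide insights into the advantages and disadvantages of each". Under Randomization of providers, "providers will be randomized in a 1:1:1 manner to one of three implementation strategies". Under Outcome measures, sustainability is determined by "comparing the frequency of COAST platform use by the trained providers across the three groups" at 3, 6 and 12 months.

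**What is specified.** In Statistical analyses plan and power calculations:

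- Reach and adoption: "we will use a test for two proportions to determine whether reach and adoption differ between COAST versus COAST+EF and COAST+EF/IF". Power is given for 8 providers against 16.
- Sustainability: a generalized linear mixed model will "regress number of interactions on group (COAST versus COAST+) and time", with a group-by-time interaction. Power is again given for 8 against 16.
- EF is set against EF/IF only in the non-inferiority test on change in the Insomnia Severity Index, a patient outcome.

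The first hypothesis, in both sections where it appears, sets the facilitated conditions against COAST only. It does not set EF against EF/IF on reach, adoption or sustainability.

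**The concern.** In a hybrid type 3 trial the implementation outcomes are the main object of study. The Trial design section says the design was chosen because it centres on comparing implementation methods, and it expects insight into which strategies are most cost-effective. The practical question is whether to add an internal champion to external facilitation. A two-level group variable cannot answer it.

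Pooling has two consequences. If only one facilitated arm works, averaging it with an inert arm halves the contrast and the test may miss it. If the pooled test is nevertheless positive, the result is attributed to both strategies and an ineffective one could be rolled out. The sections also disagree directly on sustainability: Outcome measures compares three groups and the analysis section compares two.

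**Working it through.** **Inputs, all from Statistical analyses plan and power calculations.** 8 COAST and 16 COAST+ providers; 6 or 12 repeated measures; autocorrelation 0.60–0.80; power 0.80; alpha 0.05; COAST reach/adoption rate 0.50–0.60. Stated detectable differences: 0.99–1.11 (6 measures), 0.97–1.10 (12 measures) and 0.39–0.46 (proportions). The article gives no unit for the sustainability differences and no sidedness for alpha. SD units and a two-sided test are assumed.

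**Step 1: is the specified test pooled?** The wording for reach and adoption could mean two separate contrasts, so the stated figures were reproduced both ways.

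Sustainability, compound symmetry, normal quantiles: difference = (1.960 + 0.842) × √[v × (1/n₁ + 1/n₂)], with v = (1 + (m − 1)ρ)/m.

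| m | ρ | v | 8 v 16 | Stated | 8 v 8 |
|---|---|---|---|---|---|
| 6 | 0.60 | 0.667 | 0.991 | 0.99 | 1.144 |
| 6 | 0.80 | 0.833 | 1.107 | 1.11 | 1.279 |
| 12 | 0.60 | 0.633 | 0.965 | 0.97 | 1.115 |
| 12 | 0.80 | 0.817 | 1.096 | 1.10 | 1.266 |

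Adoption/reach, two-sided pooled-variance z-test with exact binomial enumeration: 8 v 16 gives 0.460 at a COAST rate of 0.50 and 0.387 at 0.60, against the stated 0.46 and 0.39. With 8 v 8 there is no solution at 0.80 power.

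Every stated figure matches 8 v 16 and none matches 8 v 8. The planned tests are pooled.

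**Step 2: one facilitated arm inert, the other with the full stated difference D.** The pooled effect is D/2.

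- Sustainability: by construction D/SE = 2.802. Power = Φ(2.802/2 − 1.960) = Φ(−0.559) ≈ 0.29, down from 0.80. This holds for every m and ρ above.
- Adoption, by enumeration: about 0.22 (0.50, +0.46) and 0.20 (0.60, +0.39).

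**Step 3: what separate contrasts can offer (8 v 8, unadjusted).**

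- Sustainability: the standard error grows by √(0.25/0.1875) = 1.155. At D, power = Φ(2.802/1.155 − 1.960) = Φ(0.466) ≈ 0.68. The detectable difference is about 1.11–1.28. With Bonferroni for two contrasts it is about 1.23–1.41.
- Adoption: if all 8 facilitated providers adopt, the z-test rejects only when at most 4 of 8 COAST providers adopt (4 of 8: z = 0.50/√(0.75 × 0.25 × 0.25) = 2.31; 5 of 8: z = 0.375/√(0.8125 × 0.1875 × 0.25) = 1.92). Power is therefore at most P(X ≤ 4) = 0.64 at a COAST rate of 0.50, or 0.41 at 0.60. A power of 0.80 is out of reach.

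**Step 4: which outcomes can be compared by arm?** Outcome measures defines provider reach as consent plus completed COAST training, over providers informed. Randomization of providers places allocation after training and familiarization. Provider reach is thus settled before arms exist, and no contrast by arm, pooled or separate, is meaningful. Patient reach, adoption and sustainability arise afterwards and can be compared.

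**The case against.** The strongest defence is that the pooled test matches the hypothesis. The first hypothesis asks only whether facilitation beats no facilitation, and the sole EF versus EF/IF hypothesis concerns insomnia severity, where the article gives a margin, a decision rule and power. With 24 providers, 8 versus 16 is a reasonable headline test. If both facilitated arms work equally at the stated difference, it has power 0.80 against 0.68 for a separate contrast. All of this stands, so pooling as such is not the fault.

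It can also be said that a condensed article may leave secondary pairwise estimates to a fuller document. That too stands as far as mere silence goes. But the article is not silent: it fixes a two-level group variable where its own outcome definition calls for three groups.

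A reader might go further and infer that the trial never intends to compare the three strategies on implementation outcomes. The article does not support this, because Outcome measures does promise a three-group comparison for sustainability. The fault is that the specified model does not deliver it.

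A reader might also infer that separate contrasts would be well powered. That would need a difference larger than any the article assumes. At its own difference they reach 0.68 for sustainability, and for adoption they cannot reach 0.80.

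**Conclusion.** The point holds as an inconsistency between the stated aim and the specified analysis. The aim and the sustainability definition require a three-group comparison. The models as written yield no arm-specific and no EF versus EF/IF estimate on patient reach, adoption or sustainability.

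The loss of pooled power to about 0.29 for sustainability and 0.20–0.22 for adoption is the case of one wholly inert arm and one arm at the article's own detectable difference. It is the unfavourable end for pooling, not a forecast. It rests on SD units, two-sided alpha, compound symmetry and the normal quantiles that reproduce the stated figures. The misattribution risk needs no such assumptions: no pooled result can say which facilitated arm produced it.

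**What to change.** Reconcile the analysis section with the objective and with Outcome measures:

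- Keep COAST+ versus COAST as the powered headline test of the first hypothesis.
- Enter arm as a three-level factor for sustainability, adoption and patient reach.
- Report EF minus COAST, EF/IF minus COAST and EF/IF minus EF, each with a 95% confidence interval. Label all three as estimation, since each rests on 8 versus 8 providers, and do not read a non-significant difference as equivalence.
- State that provider reach is described overall and not compared by arm.

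The cost is a few lines of analysis text and no extra providers or patients. The downside is that the pairwise intervals will be wide, least informatively for adoption, and must be presented as such.

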## Statistical analyses plan and power calculations

Preliminary data analyses (e.g., descriptive statistics, correlations, principal component analysis) will be performed prior to hypothesis testing to check for collinearity of covariates and outcome measures, to ensure completeness and accuracy of data, and to evaluate distributions. Missing observations will be investigated to determine the underlying mechanism (missing at random, completely at random, not at random) so that appropriate methods for handling the missing data can be employed. Namely, if data are missing at random, we will use multiple imputation (MI) to ensure that any individuals with missing covariates or outcome data can be included in the analysis sample. However, if data are found to be missing not at random, we will use methods that explicitly model this type of nonrandom missingness (e.g., pattern mixture models) and perform sensitivity analyses evaluating the impact of the missingness. Power was computed using PASS statistical software and documentation. Each model will include covariates including study site, patient age and sex, military rank, and use of psychotropic medication (yes/no). Masked data will be provided to the biostatistician who will perform the analyses. Randomization will be unmasked only after analyses are finalized.

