The second hypothesis is that COAST+EF and COAST+EF/IF will yield greater improvements in patient insomnia symptom severity than COAST only over the acute 6-week intervention period. We will compute the change in ISI from baseline to 6 weeks (∆ISI = baseline ISI − 6-week ISI), with higher ∆ISI values indicating a greater improvement over time. We will use a mixed effects model to regress ∆ISI on group, accounting for nesting within providers through a random effect and including relevant covariates. We will extract estimates from the model to compute the standardized mean difference *d* [70, 71] and 95% confidence interval between COAST and COAST+ (EF; EF/IF) accounting for patients nested within providers. Second, using a mixed effects model with a random clinician effect, we will regress ISI at baseline and 6 weeks of treatment (COAST versus COAST+EF and COAST+EF/IF), time, and their interaction, controlling for relevant covariates. A significant treatment-by-time effect will indicate that the change in ISI differs between COAST and COAST+EF and COAST+EF/IF. Assuming an average of 12 providers per group (8 in COAST and 16 in COAST+EF and COAST+EF/IF) and 36 patients per clinician, we expect 0.80 power (alpha = 0.05) to detect a standardized mean difference of 0.232 between groups. We will also evaluate the extent to which COAST+EF is not inferior to COAST+EF/IF as measured by changes on the ISI over the acute 6-week intervention period. This non-inferiority hypothesis will be tested with the general form—H_0_: COAST+EF is inferior to COAST+EF/IF versus H_1_: COAST+EF is non-inferior to COAST+EF/IF. Using the methods described above, we will compute the standardized mean difference *d* and 95% confidence interval [*d* (95% CI)] for COAST+EF − COAST+EF/IF of ∆ISI. As positive values of ∆ISI indicate more improvement, a positive *d* is in favor of COAST+EF and a negative *d* is in favor of COAST+EF/IF. We will use a non-inferiority margin (NIM) of − 0.50 and declare COAST+EF to be non-inferior to COAST+EF/IF if the lower bound of the 95% CI for *d* is > − 0.50. We will declare COAST+EF to be inferior to COAST+EF/IF if the lower bound of the 95% CI for *d* is ≤ − 0.50. For example, if *d* (95% CI) = − 0.10 (− 0.40, 0.20), we would declare COAST+EF as non-inferior to COAST+EF/IF because − 0.40 > − 0.50. However, if *d* (95%CI) = − 0.40 (− 0.70, − 0.10), we will declare COAST+EF to be inferior because − 0.70 ≤ − 0.50. These one-sided decision rules equate to requiring the effect size of the COAST+EF to COAST+EF/IF comparison to have no more than moderate strength (|d| = 0. 5), in favor of COAST+EF/IF. The NIM of |d| = 0.5 set to determine non-inferiority is stringent as it represents 50% of the effect size reported in recent meta-analyses [50, 72, 73]. Assuming 8 providers per group and 36 patients per clinician, an intra-class correlation of 0.01 [74], a non-inferiority margin of 0.50, and a true difference of δ = 0, we expect > 0.99 power to reject our null hypothesis and conclude that COAST+EF is non-inferior to COAST+IF/EF.

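### The second ISI model names only a random clinician effect, so its treatment-by-time standard error is generally wrong, and the one explicit superiority rule rests on that model

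*Protocol article*

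**What the plan says.** All of this is in the Protocol article, section Statistical analyses plan and power calculations.

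- **First ISI analysis:** "We will use a mixed effects model to regress ∆ISI on group, accounting for nesting within providers through a random effect and including relevant covariates". It supplies the standardized mean difference d and its 95% confidence interval. The non-inferiority comparison of COAST+EF with COAST+EF/IF is defined on the same change score.
- **Second ISI analysis:** "using a mixed effects model with a random clinician effect, we will regress ISI at baseline and 6 weeks of treatment", on treatment, time and their interaction, with covariates. Its decision rule is: "A significant treatment-by-time effect will indicate that the change in ISI differs between COAST and COAST+EF and COAST+EF/IF".
- **Covariates:** "Each model will include covariates including study site, patient age and sex, military rank, and use of psychotropic medication (yes/no". Baseline ISI is not named.
- **Power:** the superiority calculation treats the 8 and 16 providers as 12 in each group on average, each with 36 patients. Its result is stated as follows: "we expect 0.80 power (alpha = 0.05) to detect a standardized mean difference of 0.232 between groups". The non-inferiority calculation adds "an intra-class correlation of 0.01".

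For the second ISI analysis the article names no patient effect, no within-patient covariance and no clinician-by-time effect. The sustainability model in the same section does name a random time term beside its random intercept. The article does not say which ISI analysis decides the hypothesis if the two disagree.

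**The concern.** Each patient contributes two ISI values to the second model. If a clinician intercept is the only random term, two errors enter the SE of the treatment-by-time contrast, in opposite directions.

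- A patient's baseline and 6-week scores are treated as independent given the clinician. The positive correlation between them, which reduces the variance of a change, is not used, so the SE is too large.
- A clinician intercept is common to both times and cancels out of the change. Differences between clinicians in how much their patients improve are therefore ignored. Providers are the randomized unit (section Trial design), so this makes the SE too small.

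The article's only explicit significance statement for superiority on ISI comes from this model. With two time points and complete data, a correctly specified repeated-measures model estimates the same contrast as the change-score model. A disagreement between the two analyses would then be mostly an artefact of the SE, with no rule for resolving it.

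**Working it through.** **Inputs.** From the article: 8 and 16 providers with 36 patients each, so 288 and 576 patients; alpha 0.05 (two-sided assumed); target d = 0.232; ICC 0.01, stated for non-inferiority and assumed here to apply to the change score. Not in the article: rho, the correlation between baseline and 6-week ISI, varied from 0.2 to 0.7. Equal variances at both times and no dropout are assumed.

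**1. The article's own figures.** Design effect = 1 + 35 × 0.01 = 1.35.
- Superiority, 12 v 12 providers: SE = sqrt(1.35 × 2/432) = 0.0791. A noncentral t on 22 df gives a detectable d of 0.2318, which matches 0.232.
- Non-inferiority, 8 v 8 providers, margin 0.50, true difference 0: SE = sqrt(1.35 × 2/288) = 0.0968, power 0.998 to 0.999, which matches > 0.99.
- Benchmark for the actual 8 v 16 split: SE = sqrt(1.35 × (1/288 + 1/576)) = 0.0839, power at 0.232 = 0.79 (normal approximation).

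None of these figures depends on the second model.

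**2. SE of the second model as written.** Per patient, the model takes the variance of a change as 2σ². The true variance is 2(1 − rho)σ², and clustering of change multiplies the variance of the contrast by 1 + 35 × ICC. Hence, approximately,

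r = model SE / true SE = sqrt(1 / ((1 − rho)(1 + 35 × ICC))).

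Type I error = 2(1 − Φ(1.96 r)). Power = Φ(0.232/0.0839 − 1.96 r).

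| rho | r at ICC 0.01 | Type I error | Power at d = 0.232 |
|---|---|---|---|
| 0.2 | sqrt(1/(0.8 × 1.35)) = 0.96 | 0.059 | 0.81 |
| 0.3 | sqrt(1/(0.7 × 1.35)) = 1.03 | 0.044 | 0.77 |
| 0.5 | sqrt(1/(0.5 × 1.35)) = 1.22 | 0.017 | 0.65 |
| 0.7 | sqrt(1/(0.3 × 1.35)) = 1.57 | 0.002 | 0.38 |
| correct SE | 1 | 0.05 | 0.79 |

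The two errors cancel where (1 − rho) × 1.35 = 1, that is at rho = 0.26.

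**3. A larger ICC of change.** At 0.05 the design effect is 2.75. With rho 0.3, r = sqrt(1/(0.7 × 2.75)) = 0.72 and type I error is 0.16. With rho 0.5, r = 0.85 and type I error is 0.095. With rho 0.7, r = 1.10 and the test is still conservative (0.031).

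**4. Simulation.** Mixed models were fitted to 8 v 16 providers with 36 patients each, in 150 to 300 runs per setting.
- ICC 0.01, rho 0.5: second-model SE 0.101 against an empirical SD of 0.082; null rejection 0.020; power 0.69 in one set of runs and 0.67 in another.
- ICC 0.01, rho 0.7: SE 0.101 against 0.066; null rejection 0.000; power 0.35.
- ICC 0.05, rho 0.3: SE 0.102 against 0.151; null rejection 0.18.
- Change-score model at ICC 0.01, rho 0.5: SE 0.084 against 0.082; null rejection 0.043; mean estimate 0.233 for a true 0.233.

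**5. Baseline ISI in the change-score model.** Adjustment multiplies the patient-level variance by (1 − rho²)/(2(1 − rho)) = (1 + rho)/2. The 1.35 splits into 0.99 at patient level and 36 × 0.01 = 0.36 at provider level. If the provider part is left unchanged, the detectable difference is multiplied by sqrt((0.99 × 0.75 + 0.36)/1.35) = 0.90 at rho 0.5 and sqrt((0.99 × 0.65 + 0.36)/1.35) = 0.86 at rho 0.3. Simulation at rho 0.5 gave an SE of 0.077 against 0.084, about 8% less. The gain is therefore roughly 8 to 14%.

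**The case against.** The strongest reply is that the article never says the clinician effect is the only random term. A journal article may leave the covariance structure to an analysis plan, and the change-score model comes first and supplies d, its interval and the non-inferiority decision. Superiority on ISI is also the second hypothesis in a trial designed mainly to compare implementation strategies. Much of this stands. It limits the consequence to one superiority test and would make the point a clarification if a fuller plan supplies the missing terms. It does not remove the point: the article does state the random part of this model, is more explicit for the sustainability model, and attaches its superiority rule here.

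A second reply is that the covariate list is open. It is introduced as non-exhaustive, and the first ISI model is described as "accounting for nesting within providers through a random effect and including relevant covariates", so baseline ISI is not excluded. That stands. Naming baseline ISI is an improvement in precision, not the correction of an error.

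A third reply is that serious false-positive rates need inputs the article does not give. That also stands: at the stated ICC of 0.01, type I error runs from near nominal to very conservative over the correlations examined.

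**Conclusion.** The point holds for the second ISI model. As written, its treatment-by-time SE is right only by coincidence, near rho 0.26 at an ICC of 0.01. For rho of 0.5 or more at that ICC the likely harm is lost power: 0.65 or less where 0.79 is available. These sizes rest on the assumed rho, on applying the ICC of 0.01 to change, on equal variances and on complete data.

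Three stronger readings are tempting and are not supported.

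- **That both ISI models are mis-specified.** The change-score model has one value per patient and a random effect at the level of randomization. It held its error rate and was unbiased in simulation at ICC 0.01. Leaving out baseline ISI costs precision and leaves chance imbalance unadjusted, but it does not invalidate the test.
- **That the superiority test has a type I error of 10% or more.** This needs an ICC of change well above the stated 0.01, for example 0.05, together with a low rho.
- **That the change score is biased because providers know their arm before they enroll patients and make the final inclusion decision.** Baseline severity could differ by arm for this reason, but the article does not show that it will. Under such selection, change-score analysis and baseline adjustment rest on different assumptions, so adjustment is not automatically the remedy.

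The non-inferiority conclusion does not depend on the second model.

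**What to change.** Name one primary analysis for ISI superiority: change in ISI (or 6-week ISI) on group, with a random provider effect, the listed covariates and baseline ISI stated explicitly. Use small-sample degrees of freedom (Kenward-Roger or Satterthwaite), because only 24 providers carry the comparison. Attach the significance rule to this model and take the non-inferiority contrast from it as well.

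Then either drop the repeated-measures model, or add a patient effect (or unstructured within-patient covariance) and a clinician-by-time random effect and label it supportive.

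The cost is analysis wording. Baseline ISI is already collected, and neither the sample size nor the visit schedule changes.

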## Selection criteria and enrollment of participating providers and patients

The trial aims to recruit at least 24 providers (clinicians and health coaches) who currently provide services in behavioral health to service members, their dependents, and beneficiaries across Navy Medical Forces Pacific (NMFP). The participating military treatment facilities (MTFs) and affiliated clinics are all located in Southern California. We aim to enroll providers who already deliver cognitive-behavioral health interventions as part of their regular practices, including behavioral sleep interventions like CBTI.

Each participating provider will enroll at least 36 patients over the course of 12 months, for a total minimum patient sample of 864. Across participating sites, providers will be informed of the trial through emails, newsletters, flyers, word of mouth, notifications sent to and by clinic leaders and/or department administrators, and flyers posted around the facilities and clinics. Providers will also be invited to participate in two remote half-day training workshops for which continuing education credits will be offered. The first segment of the training will be open to all interested providers at each site and focused on principles and practices of BSM.

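### The 0.80 power for an ISI difference of 0.232 comes from averaging 8 and 16 providers to 12 per group, and it counts patients from COAST-only providers whom the plan elsewhere expects not to adopt

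*Protocol article*

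**What the plan says.** All places are in the Protocol article.

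- **Randomization of providers:** "providers will be randomized in a 1:1:1 manner to one of three implementation strategies". With 24 providers this gives 8 per arm, so COAST only against the two facilitated arms pooled is 8 versus 16.
- **Selection criteria and enrollment:** "Each participating provider will enroll at least 36 patients over the course of 12 months, for a total minimum patient sample of 864".
- **Statistical analyses plan and power calculations, second hypothesis:** "Assuming an average of 12 providers per group (8 in COAST and 16 in COAST+EF and COAST+EF/IF) and 36 patients per clinician", followed by "we expect 0.80 power (alpha = 0.05) to detect a standardized mean difference of 0.232 between groups". This sentence names no intra-class correlation. The non-inferiority calculation later in the section uses "an intra-class correlation of 0.01".
- **Same section, first hypothesis:** power for the provider outcomes is worked out from "a reach and adoption between 0.50 and 0.60 in COAST".
- **Outcome measures:** adoption is the share of trained providers who begin using COAST with patients, meaning that they give a patient an app code. Trained non-users stay in the denominator.
- **Discussion:** a clinician who withdraws is replaced. Nothing similar is said of a trained provider who stays in the trial but enrolls nobody.

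**The concern.** Two inputs to the ISI power statement do not fit the design.

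The first is the averaging. The variance of a difference between two unequal groups depends on the sum of the reciprocals of their sizes. Replacing 8 and 16 by 12 and 12 keeps the total but understates the variance.

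The second is that the two hypotheses are planned on different pictures of the COAST-only arm. For the first, 40 to 50% of its providers may never start a patient. For the second, all 8 deliver 36 patients each. A provider who starts no patient supplies no ISI change, and the loss falls on the smaller group, where it costs most precision.

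The ISI is the primary patient-centered outcome, and the results are meant to guide policy. A reader who finds no clear difference would weigh it against a claimed 0.80 power at 0.232 that the design does not deliver.

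**Working it through.** **Inputs.** Providers 12/12 (as averaged) or 8/16 (as randomized); 36 patients per provider; alpha 0.05, taken as two-sided because sidedness is not stated; intra-class correlation 0.01, borrowed from the non-inferiority calculation; outcome SD set to 1, so the difference is in SD units.

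**Formulae.**
- Design effect: DE = 1 + (36 − 1) × 0.01 = 1.35.
- SE = sqrt[(DE/36) × (1/k1 + 1/k2)], with DE/36 = 0.0375.
- Power from the noncentral t distribution with k1 + k2 − 2 degrees of freedom and noncentrality d/SE. The detectable d is the value giving 0.80.

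**Step 1: reproduce the stated figure.** At 12 versus 12, 1/12 + 1/12 = 0.1667 and SE = sqrt(0.0375 × 0.1667) = 0.0791. On 22 degrees of freedom, 0.80 power needs d = 2.932 × SE = 0.2318. Power at 0.232 is 0.801. This matches 0.232 to three decimals. The normal approximation gives 0.2215 and does not match.

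**Step 2: use the actual split.** At 8 versus 16, 1/8 + 1/16 = 0.1875, which equals 2/10.67, so the design is worth about 10.7 providers per group. SE = sqrt(0.0375 × 0.1875) = 0.0839. Detectable d = 2.932 × 0.0839 = 0.246, and power at 0.232 is 0.753. By normal approximation these are 0.235 and 0.790.

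**Step 3: apply the COAST-only adoption rate.** 0.50 × 8 = 4.0 and 0.60 × 8 = 4.8, so about 4 or 5 providers are active. All 16 facilitated providers are taken as active, which is the most favorable case.

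| Active providers | SE | df | Detectable d | Power at 0.232 | Power, normal approx. |
|---|---|---|---|---|---|
| 12 vs 12 (as averaged) | 0.0791 | 22 | 0.232 | 0.80 | 0.84 |
| 8 vs 16 (as randomized) | 0.0839 | 22 | 0.246 | 0.75 | 0.79 |
| 5 vs 16 | 0.0992 | 19 | 0.293 | 0.60 | 0.65 |
| 4 vs 16 | 0.1083 | 18 | 0.321 | 0.53 | 0.57 |

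**Step 4: could higher enrollment per adopter make up for it?** The 36 is a minimum, so suppose the active providers still reach 864 in total. At 5 versus 16 that is 864/21 = 41.1 patients each, with power 0.64. At 4 versus 16 it is 864/20 = 43.2 each, with power 0.58. What is missing is COAST-only providers, and extra patients elsewhere only partly replace them.

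**The case against.** The averaging error is small and open to view: the 8/16 split is printed in the same sentence, and by normal approximation power is still 0.79. This stands. The averaging alone does not put power far below 0.80.

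A reader might infer that 0.232 can arise only from 12 versus 12. The document does not support that, because the superiority sentence names no intra-class correlation. With the t method, 8 versus 16 would also give 0.232 at an intra-class correlation of about 0.006; with the normal approximation, at about 0.009. Neither value is printed, and 12 versus 12 at the one printed value matches exactly, so it is the likely source but not a proven one. Covariate adjustment could also help. (0.232/0.246)² = 0.89, so covariates explaining about 11% of the variance (an assumption) would restore 0.80 at 8 versus 16.

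A reader might also infer that the plan assumes near-complete adoption in the facilitated arms, by adding 0.39–0.46 to 0.50–0.60. Those increments are detectable differences, not expected rates. The 0.50–0.60 itself is a planning value given jointly for reach and adoption, so the adoption figures above are a scenario built on the plan's own value, not a forecast.

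Two further extensions do not hold. Each facilitated arm alone against COAST only (8 versus 8) has less power, but the power statement covers the pooled contrast and is not contradicted by that. The article gives no dropout rate, and a condensed article may leave that allowance to the full protocol.

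Finally, the plan will report d with a 95% confidence interval, which shows the precision achieved, and the trial's main focus is implementation. Both points limit the harm. Neither makes the stated power correct. Replacement of withdrawn providers and the stated minimums soften the adoption conflict, but replacement is not extended to trained non-users.

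**Conclusion.** The concern holds in two parts of different size.

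1. **Averaging.** By the method that reproduces the protocol's figure, the 8 versus 16 contrast has power 0.75 at 0.232, not 0.80, and a detectable difference of 0.246. This is a modest error. It rests on an intra-class correlation of 0.01 and a two-sided test.
2. **Adoption.** The ISI calculation needs 36 patients from all 8 COAST-only providers, while the first hypothesis is planned on 0.50 to 0.60 reach and adoption in that arm. Both cannot hold. With 4 or 5 of the 8 active and all 16 facilitated providers active, power at 0.232 is about 0.53 to 0.60 and the detectable difference about 0.29 to 0.32.

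The second part matters more, but it is conditional on the adoption scenario. It should not be read as the power that the trial will certainly have. The calculation behind the > 0.99 non-inferiority power is not affected by the averaging: 8 versus 8 providers gives 0.998 by the t method.

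**What to change.** In the power paragraph for the second hypothesis:

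- Replace the average of 12 per group with the 8 versus 16 contrast, say that it is COAST only against the pooled facilitated arms, and state 0.80 power for a difference of about 0.246 with full adoption and follow-up.
- Name the intra-class correlation used for this calculation. If it was not 0.01, give the value and recompute.
- Add the detectable difference under the COAST-only adoption rate used for the first hypothesis, about 0.29 to 0.32, so that both hypotheses rest on one adoption assumption. If adoption is expected to be higher, change it in both places.

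This changes stated figures only. No patients, providers, analyses or decision rules are added. The cost is a less favorable statement of sensitivity.
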